### Data management

2.8

Data collection and management will be carried out by a collaboration of research associates, coordinators and clinicians. All the investigators will undergo standard operating procedure (SOP) training based on the study protocol. During the trial, subject recruitment, intervention, follow-up, data collection and data management will be performed in strict accordance with the SOPs.

The clinicians will be responsible for the baseline and outcome examinations, including SQD symptom assessments, biological sample collections, and laboratory examinations. All these data will be entered on pilot-tested case report forms. The research coordinators will be student volunteers from Jiangxi University of Traditional Chinese Medicine and will be responsible for contacting patients and helping with communication between patients and doctors. We will assign to each study center a research associate selected from researchers at Jiangxi University of Traditional Chinese Medicine who will be responsible for monitoring the follow-up process, standard performance, patient compliance, and completeness of data collection. We will develop a specialized computer system for data entry that will support data query and verification. Once verified, data will be locked and accessible to only data analysts during the data analysis period. In special cases and emergency conditions, such as SAEs, the database will be temporarily accessible, and data for the corresponding participant will be unblinded.

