### Randomization and blinding

2.3

Patients who pass the eligibility assessment will be randomly and proportionally divided into four groups: Group A, B, C, and D. We generated a block randomization sequence using Microsoft Excel that was saved as enciphered data. For allocation concealment, we will adopt centralized random assignment. Independent researchers who do not participate in trial procedures other than the randomization process will recode the random sequence into continuous numbers and label the boxes of trial samples. Samples will be allocated sequentially to participants. In this way, no one will know the group into which the next participant will be assigned.

This trial will have 3 intervention periods: standard treatment period, maintenance treatment period, and recuperation treatment period. The standard treatment period will be open-label. During the maintenance and recuperation treatment period, the clinicians, patients, outcome assessors, and data collectors will be blinded in terms of the assignment of HGMX or placebo but the administration of rabeprazole will be open-label. Except in instances of a severe AE, all the participants, medical providers, data collectors, and outcome reviewers will strictly adhere to the blinded de∗sign until the trial has been completed. In addition, an independent committee will supervise the allocation concealment and blinding, and if blinding is violated, the corresponding patient will be excluded. Figure 1 gives an overview of the study design and procedures.

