#### Safety outcomes

2.5.3

1.AEs, which will be assessed in 2 ways: significant abnormality (below or above twice the normal reference range) in the results of routine blood, urine or stool examinations, liver or kidney function tests, or electrocardiogram; AEs reported by clinicians and patients.2.Severe AEs (SAEs), which are defined as AEs that are life-threatening or lead to admission to the intensive care unit, prolonged hospitalization, or physical or mental disability. Once an SAE occurs, the principal investigator will report it to the hospital institutional review board and submit the appropriate paperwork to the Food and Drug Administration, Department of Jiangxi Province, within 24 hours.3.Treatment-related AEs, which must meet all the following criteria: the AE has reasonable time causality with treatment administration; comorbidities and co-interventions are not related to the AE; the symptoms of the AE improved or recovered when treatment was stopped; and the causality can be explained by pharmacological, biological, or phenomenological mechanisms.4.Withdrawal owing to AEs.

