### Sample size estimation

2.9

The main objective of this trial is to assess the effects of HGMX compared with placebo on the total effective rate. Therefore, the sample size estimation is based on the formula for a superiority design.^[24]^ Because there are no previous studies available for reference, we estimated a *P* of .85 (total effective rate in the two groups receiving HGMX) and a *P*_0_ of .65 (total effective rate in the 2 groups receiving placebo) according to the results of our pilot survey and expert opinions. In addition, we adopted a type I error (α) of 0.05, a type II error (β) of 0.2, and a maximum drop-out rate of 15%. Based on these assumptions and our funding constraints, we computed a sample size of 360, with 90 in each group.

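### A serious adverse event by itself opens the patient's allocation, so the treatment-related rating of SAEs from week 3 on may be made by someone who knows HGMX versus placebo

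*Protocol article*

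**What the plan says.** Section 2.8 (Data management), after describing the locking of verified data, adds: "In special cases and emergency conditions, such as SAEs, the database will be temporarily accessible, and data for the corresponding participant will be unblinded".

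Section 2.3 (Randomization and blinding) sets out the masking and one exception to it: "Except in instances of a severe AE, all the participants, medical providers, data collectors, and outcome reviewers will strictly adhere". The rest of that sentence says that the masking lasts through trial completion. It concerns the study food only. In the maintenance and recuperation periods, patients and those who treat, assess or record them "will be blinded in terms of the assignment of HGMX or placebo but the administration of rabeprazole will be open-label". The same section says that a patient whose blinding is violated will be excluded.

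Section 2.5.3 (Safety outcomes) uses SAE as the abbreviation for severe AE, so 2.3 and 2.8 refer to the same events. It defines them as "AEs that are life-threatening or lead to admission to the intensive care unit, prolonged hospitalization, or physical or mental disability". It lists as a separate safety outcome "Treatment-related AEs, which must meet all the following criteria". There are four criteria: a reasonable time relation, no link to comorbidities or co-interventions, "the symptoms of the AE improved or recovered when treatment was stopped", and, as the fourth, that "the causality can be explained by pharmacological, biological, or phenomenological mechanisms".

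**The concern.** The event that most needs a masked causality judgement is also the event that opens the code. The wording in 2.8 is mandatory once the trigger is met, and an SAE is the named example of the trigger. Neither section asks whether the patient's care depends on the allocation, or says to whom it may be disclosed.

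Two things are at stake. One is the treatment-related AE outcome for serious events. An assessor who knows the arm can lean either way: dismissing a placebo patient's event, or blaming or excusing HGMX. The protocol voices a prior expectation here, since the Introduction anticipates a good safety profile and reports no related AEs in 3 years of post-market monitoring. The other is the later grading of efficacy in the same patients. Rabeprazole is open-label, so the HGMX/placebo mask is the only one the trial has.

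**Working it through.** No figure in the plan bears on this point, so the check sets the texts side by side.

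**1. Trigger.** Section 2.8 covers special cases and emergency conditions, with SAEs as the example, and says that unblinding will follow. Section 2.3 names the severe AE as its only exception, with no qualifier. Read together, an SAE is sufficient to open the code, and no test of need is stated.

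**2. Breadth of the trigger.** The SAE definition includes prolonged hospitalization and disability, whatever the cause. Events whose management does not turn on HGMX versus placebo therefore qualify.

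**3. Which causality criteria can be swayed.**

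| Criterion in 2.5.3 | Open to influence by knowing the arm? | When it can be judged |
|---|---|---|
| Time relation | Little; rests on dates | At the event |
| No other cause (comorbidity, co-intervention) | Yes; judgement | At the event |
| Improvement after stopping | Some | Only after treatment has stopped |
| Explicable mechanism | Yes; judgement | At the event |

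All four must be met. Knowing the arm can therefore change a rating only for an SAE that could satisfy the remaining criteria.

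**4. Time window.** Weeks 1 to 2 are open-label and involve neither HGMX nor placebo (2.4.1). The point concerns SAEs from week 3 on.

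**5. Outcomes outside the problem.** Counts of AEs and of SAEs do not use the causality criteria. Non-serious AEs do not trigger the exception.

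**6. Later efficacy grading.** Under 2.8 the clinicians carry out the SQD symptom assessment, which is a primary outcome, at all follow-up visits. Gastroscopy is at weeks 12, 26, 52 and 104, and histology at weeks 12 and 26 (2.6). A patient unblinded for an SAE who remains in follow-up may be graded by someone who knows the arm. Patients with acute bleeding or perforation, or who withdraw owing to AEs, discontinue under 2.7 and largely drop out of this concern.

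**7. Collision with the exclusion rule.** Section 2.3 excludes patients whose blinding is violated and does not say whether SAE unblinding counts. Section 2.10 defines the safety population as everyone treated at least once. If SAE unblinding counted as a violation, patients with the most serious events could be removed from a population meant to contain them.

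**8. Scale, for illustration only.** The documents give no SAE rate. If 2% to 5% of the 360 patients had an SAE over the 104 weeks (my assumption):
- 0.02 × 360 = 7.2, about 7 patients;
- 0.05 × 360 = 18 patients;
- with equal rates by arm, half would be on placebo: 3.6 to 9.

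These are patients unblinded, not ratings changed. The span also includes weeks 1 to 2, which carry no HGMX or placebo, and weeks 53 to 104, when all interventions have stopped. The number of ratings changed would be smaller, possibly zero, and cannot be derived.

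**The case against.** The strongest reply is that 2.8 is only an access exception for emergencies, already restricted to the one participant concerned. On this view 2.3 merely carves out a case from a general rule, an independent committee oversees blinding, and the order of code-break and causality forms belongs in SOPs or the full protocol. Part of this stands. The phrase in 2.8 could be read as only those SAEs that are emergencies, and silence about form-filling order in a condensed article would not by itself be a finding. But the rule that is printed makes the SAE the trigger, and the unqualified exception in 2.3 favours the broad reading. If the narrow one was meant, the text should say so.

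Three stronger readings are tempting, and the documents do not support them.
- A reader might infer from 2.3 that all the listed roles are told the allocation after an SAE. The text lifts the obligation but does not say who sees the opened data or who judges causality. It supports no more than that the assessor may know.
- A reader might infer that every SAE unblinded in this way biases the relatedness count. An SAE plainly due to something else, such as a fracture with a long stay, would be unrelated in either arm.
- A reader might infer that a placebo patient's event fails the mechanism criterion automatically. Treatment in 2.5.3 is not limited to HGMX. All patients receive rabeprazole and bismuth in weeks 1 to 2, and Group D takes rabeprazole with placebo in weeks 3 to 6.

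**Conclusion.** The concern holds in limited form. As written, 2.3 and 2.8 let an SAE open the allocation without reference to need and without limiting disclosure. For SAEs from week 3 on that could meet the other causality criteria, the treatment-related rating may be made with knowledge of HGMX versus placebo. Later SQD or endoscopic grading of such patients who stay in the trial may be unmasked too. Non-serious AEs and plain AE and SAE counts are untouched.

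The effect on the safety result cannot be quantified from the documents. The conclusion rests on reading 2.8 together with the unqualified exception in 2.3, not on any assumed SAE rate. Treatment-related SAEs may be few, in which case a few reclassified events could alter the conclusion. As the remedy is mostly wording, the change should be made.

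**What to change.** Reword 2.3 and 2.8 so that:
- an SAE does not by itself open the code, while emergency unblinding remains available;
- any code break is for the single patient, and the allocation is disclosed only to those who need it for that patient's care;
- outcome assessors and data collectors stay masked;
- the causality criteria that can be judged at the time (time relation, other causes, mechanism) are recorded and dated before the code is opened, where the emergency allows;
- the criterion on improvement after stopping, which cannot be known at that point, is completed later by existing study personnel who remain masked.

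State also in 2.3 that SAE unblinding is not a violation leading to exclusion, so that it agrees with the safety population in 2.10.

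This governs who learns the allocation and when causality is recorded. It sets no clinical rule for when an emergency code break is justified. The cost is revised wording in two sections, one date/time field on the SAE form, and one added step before a code is opened.

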### Sample size estimation

2.9

The main objective of this trial is to assess the effects of HGMX compared with placebo on the total effective rate. Therefore, the sample size estimation is based on the formula for a superiority design.^[24]^ Because there are no previous studies available for reference, we estimated a *P* of .85 (total effective rate in the two groups receiving HGMX) and a *P*_0_ of .65 (total effective rate in the 2 groups receiving placebo) according to the results of our pilot survey and expert opinions. In addition, we adopted a type I error (α) of 0.05, a type II error (β) of 0.2, and a maximum drop-out rate of 15%. Based on these assumptions and our funding constraints, we computed a sample size of 360, with 90 in each group.

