### Data analysis

2.10

The primary outcome data will be analyzed using the intention-to-treat population, in which all patients will be maintained in their initial group assignment regardless of compliance and contamination, and missing data will be imputed using the last observation carried forward method. Meanwhile, we will also conduct a sensitivity analysis with the per-protocol population. The safety outcomes will be analyzed using a safety population including all participants who received treatment at least once. Mid-term and final data analyses will be performed at the end of week 52 and 104, respectively.

Normality will be detected using the Kolmogorov-Smirnov method. Normal continuous variables will be described using the mean and standard deviation and compared using a *t* test or analysis of variance. Non-normal continuous variables will be described using the median and interquartile range and analyzed with the Mann–Whitney *U* test. Categorical variables will be presented as the frequency and percentage and compared using Pearson *χ*^2^ test. The boundary of significance for the *P* value will be .05, which will be adjusted using the O’Brien & Fleming method for multiple comparisons.

According to our factorial design, we will explore whether there exists an interaction between HGMX and rabeprazole. If there are no significant interaction effects, we will compare the main effects of HGMX and rabeprazole. In addition, we will perform subgroup analysis stratified by type of PUD (GU vs. DU) and *H pylori* infection status (yes vs no). All statistical analyses will be conducted in Stata v14.0 software.

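### The planned 360 patients do not follow from section 2.9's own inputs: for the pooled HGMX comparison that those inputs describe, about 172 would give 80% power, and 360 gives about 98%

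*Protocol article*

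**What the plan says.** Section 2.9 (Sample size estimation) sets the purpose of the calculation: "The main objective of this trial is to assess the effects of HGMX compared with placebo on the total effective rate". It gives a rate of 0.85, described as the "total effective rate in the two groups receiving HGMX", and a rate of 0.65, described as the "total effective rate in the 2 groups receiving placebo". For the error rates, "we adopted a type I error (α) of 0.05, a type II error (β) of 0.2", and drop-out is put at no more than 15%. From these assumptions and the available funding, "we computed a sample size of 360, with 90 in each group". The section refers to a cited superiority formula. It states neither a margin nor whether the test is one- or two-sided.

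Section 2.10 (Data analysis) treats the trial as factorial. Of the interaction it says "we will explore whether there exists an interaction between HGMX and rabeprazole", and if none is significant, the main effects of HGMX and rabeprazole are compared. The HGMX main effect sets Groups A and C against Groups B and D, which is 180 against 180. The section does not say what is compared if the interaction is significant. It names no comparison of A with B or of C with D.

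**The concern.** The rates in section 2.9 belong to pooled sides of two groups each, but the answer is a number per single group. If the inputs are taken as written, 360 should be the total that gives 80% power for the pooled comparison. It is about twice that total.

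A reader of section 2.9 would conclude that the trial has 80% power for a 20-point difference between HGMX and placebo. In fact it reaches that power for a clearly smaller difference. The reader also cannot tell whether 90 per group was chosen for the pooled effect, for a comparison within one rabeprazole stratum, or on other grounds. What is at stake is whether the stated planning figure is correct. The validity of the main test is not in question.

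**Working it through.** **Inputs (section 2.9):** p1 = 0.85, p0 = 0.65, difference 0.20, mean rate 0.75, alpha 0.05, power 0.80, drop-out 15%. Two-sided testing is an assumption. The test is Pearson's chi-square (section 2.10).

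**1. Size per side.**

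n = [1.96·√(2·0.75·0.25) + 0.8416·√(0.85·0.15 + 0.65·0.35)]² / 0.20²

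= [1.96·0.6124 + 0.8416·0.5958]² / 0.04 = (1.2003 + 0.5014)² / 0.04 = 72.4, so 73 evaluable.

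Enrolled: 73/0.85 = 85.9, so 86 per side.

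- As two pooled sides: 2 × 86 = 172 in total, or 43 per group.
- As a single-group size given to each of four groups: 4 × 86 = 344.

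The plan states 360. Neither reading reproduces it, but the second is much nearer.

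**2. Other formulas, enrolled per side.**

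| Variant | Per side | Total if two pooled sides |
|---|---|---|
| One-sided | 68 | 136 |
| One-sided, continuity corrected | 79 | 158 |
| Two-sided, unpooled variance | 82 | 164 |
| Two-sided, arcsine | 84 | 168 |
| Two-sided, pooled variance in null term (step 1) | 86 | 172 |
| Two-sided, pooled variance in both terms | 87 | 174 |
| Two-sided, continuity corrected | 98 | 196 |
| Two-sided, Bonferroni for 2 | 104 | 208 |
| Two-sided, Bonferroni for 6 | 133 | 266 |

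No variant gives 90 per group, and none brings the pooled total near 360. The nearest values to 90 are 86 and 87.

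**3. Power that 360 provides.** With n per side, power = Φ[(0.20·√n − 1.2003)/0.5958].

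- Pooled, after drop-out (180 × 0.85 = 153): (2.4739 − 1.2003)/0.5958 = 2.14, power 98.4%.
- Pooled, all 180 (the intention-to-treat analysis imputes missing values): (2.6833 − 1.2003)/0.5958 = 2.49, power 99.4%.
- One group against one group, after drop-out (90 × 0.85 = 76.5): (1.7493 − 1.2003)/0.5958 = 0.92, power about 82%. With all 90 it is 87.9%. This assumes that 85% and 65% hold within the stratum.

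**4. Detectable difference.** From 65%, with 153 per side, power is 78.1% for 14 points and 83.9% for 15 points. It reaches 80% at about 14.4 points.

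**5. Interaction.** The protocol gives no interaction size, so these figures are illustrations. With 76.5 per group and cell variances from 0.85 and 0.65, the standard error of the difference of differences is √[2·(0.1275 + 0.2275)/76.5] = 0.0963. Power is Φ(0.10/0.0963 − 1.96), about 18%, for a 10-point interaction, and Φ(0.20/0.0963 − 1.96), about 55%, for a 20-point interaction.

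**The case against.** Four arguments can be made for the plan.

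*Each cell may have been sized on purpose.* The main effects are compared only if the interaction is not significant. The natural alternative is HGMX against placebo within each rabeprazole stratum, where 90 per group gives about 82% power. Sizing the cells for that would be a defensible and cautious choice. This stands as a possibility. A reader might infer that the 80% fits no analysis at all, and the documents do not support that. But section 2.9 does not say that 90 was chosen for this purpose, and section 2.10 does not name the comparison.

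*The route to 360 is partly hidden.* A reader might infer that the authors took a two-group size and gave it to every arm. That cannot be shown: the two-group result is 86 to 87, and rounding up to 90 would be a guess. A superiority margin could also lead to 360. For illustration, an assumed margin of 6.5 points (two-sided) gives about 153 evaluable and 180 enrolled per pooled side. The protocol states no such margin, so this does not reconcile the stated inputs with the stated result. Funding limits would ordinarily cap a sample and do not explain doubling it.

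*The error is on the safe side.* This stands in full. The main comparison has more power than stated.

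*The interaction test is only exploratory.* This also stands. No power is claimed for it, and any figure rests on an assumed interaction size.

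**Conclusion.** The point holds for the pooled comparison. The inputs in section 2.9, read as that section defines them, lead to about 172 patients. The planned 360 give that comparison about 98% power (98.4% with 153 per side, 99.4% with 180), and about 80% power for a difference of 14 to 15 points from 65%. These figures assume a two-sided test, no margin and the stated rates. A one-sided test would need fewer patients and so widens the gap.

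Ninety per group is of the order of a one-group against one-group size and gives about 82% power within one rabeprazole stratum. The protocol leaves open whether that was the intention. A reader might infer that the trial is badly sized or its main test unsafe. The documents do not support that, because the discrepancy adds power and leaves the test, endpoint and allocation untouched. The weight is moderate: a planning statement to be corrected, with no conclusion of the trial at risk.

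**What to change.** Keep 360 and rewrite the sample size paragraph in section 2.9 so that it:

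- states whether alpha is one- or two-sided, and any superiority margin if one was used;
- says which comparison the 90 per group serves, and names the within-stratum comparison if it is the intended fallback when the interaction is significant;
- reports, if the test is two-sided and without a margin, that 180 per side (153 after 15% drop-out) give about 98% power for 85% against 65% in the pooled HGMX comparison, and about 80% power for a 14 to 15 point difference from 65%;
- reports that HGMX against placebo within one rabeprazole stratum (about 76 against 76 after drop-out) has about 82% power for the same rates.

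If a power is quoted for the exploratory interaction test, mark it as resting on assumed interaction sizes (about 18% for 10 points, about 55% for 20 points).

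The cost is one paragraph. Enrolment, allocation and analysis do not change.
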